### Ethical considerations

The study was approved by the Campania 2 Ethics Committee (Approval no. 0013474−2025, 21 May 2025). All participants will provide written informed consent. The study was registered on the Open Science Framework (DOI: https://doi.org/10.17605/OSF.IO/YHD87).

### Study status and timeline

At the time of manuscript submission, participant recruitment has not yet begun. The recruitment phase is planned to start in September 2025, with an estimated end by December 2025. Data collection will continue until March 2026, and results are expected to be available by June–July 2026. No recruitment or data collection activities have been undertaken prior to registration or submission. Qualitative interviews will be conducted with a purposive subsample of approximately 40–50 participants rather than with the entire cohort, thereby reducing the workload. Should recruitment or interview scheduling take longer than anticipated, the timeline allows for a potential three-month extension (until June 2026) to ensure adequate coverage. This contingency plan is designed to safeguard feasibility without compromising data completeness or methodological rigor.

## Expected results

The CAMP study is expected to produce a comprehensive dataset describing the clinical, functional, and social characteristics of adults with chronic illnesses residing in rural and semi-rural Southern Italy. We anticipate identifying a high prevalence of unmet needs in areas such as health-related quality of life, access to services, and perceived social support. It is expected that older age, lower education level, and geographic remoteness will be significantly associated with worse outcomes on SF-36 and Barthel Index scores.

The study also anticipates that a notable proportion of participants will report difficulties in accessing health services, with long waiting times, travel distances, and limited domiciliary support emerging as key barriers. Thematic analysis of qualitative data is expected to yield recurring patterns related to care fragmentation, lack of service integration, and caregiver burden.

These findings will allow the generation of territorial maps indicating service gaps and population clusters most at risk, thus supporting the planning of localized interventions such as the implementation of community hospitals, multidisciplinary teams, and telemedicine services.

## Discussion

This study protocol outlines a robust methodological framework for assessing the unmet health and social care needs of chronically ill patients living in underserved rural areas of Southern Italy. By applying a mixed-methods approach and integrating both validated quantitative measures and qualitative narratives, the CAMP study addresses critical knowledge gaps in the design of territorial health interventions.

The expected findings may reveal not only the extent of service accessibility issues and care fragmentation but also socio-demographic patterns that affect chronic disease management outcomes. If these expectations are confirmed, they will reinforce the need for implementing locally adapted, proximity-based models of care, such as community hospitals and telehealth services. These models are aligned with national health system reforms advocated under Italy’s PNRR, which emphasizes equitable, decentralized, and multidisciplinary care delivery.

One of the key strengths of the CAMP protocol is its replicability across similar rural or semi-rural settings, both nationally and in other European contexts. The stratified sampling and use of validated instruments enhance the generalizability of findings, while the inclusion of semi-structured interviews adds contextual depth.

Nevertheless, some limitations must be acknowledged. Being a cross-sectional observational study, causal relationships cannot be inferred. Response bias may arise from self-reported instruments and voluntary participation, potentially underrepresenting more fragile subgroups. Moreover, logistical challenges in reaching the most isolated populations may affect full territorial representation.

Despite these limitations, the CAMP study has the potential to inform actionable strategies for improving chronic care delivery, resource allocation, and integration between social and health services. It also contributes methodologically by demonstrating how mixed-methods research can support evidence-based health planning in complex territorial contexts.

Results will be disseminated through peer-reviewed open access publications and presentations at national and international conferences. Any protocol amendments or interruptions will be promptly reported to the Ethics Committee and updated in the OSF registry.

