## Materials and methods

### Aim, design and setting of the study

The CAMP study (Chronic health Assessment and Mapping of Proximity needs) is designed as a cross-sectional, observational, non-interventional study employing a mixed-methods approach. It will be conducted in multiple rural and semi-rural municipalities within the Campania region of Southern Italy, in collaboration with local health authorities and social services. For the purposes of this study, underserved rural/semi-rural areas are defined as municipalities with a medium/low population density (<150 inhabitants/km²), located more than a 30-minute drive from the nearest tertiary care hospital, and with below-average availability of health and social services, based on regional planning indicators. The classification also considers additional socioeconomic vulnerability factors, such as population aging and per capita income below the regional average. These operational criteria ensure transparency and replicability in the selection of recruitment areas.

The primary aim is to assess the health and social care needs of adults with chronic conditions residing in underserved areas, to inform future proximity-based care planning.

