### Sample size, inclusion and exclusion criteria

The sample size was calculated assuming a 30% prevalence of patients reporting significant barriers to healthcare access, with a 5% margin of error and 95% confidence level. This prevalence was adopted as a conservative assumption, consistent with recent European evidence reporting unmet healthcare needs in the range of 25–35% among chronically ill and rural populations [5; 7,8]. Considering a potential dropout or non-response rate of 20–25%, we aim to enroll approximately 400–500 participants.

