### Characteristics of participants and sample selection

Eligible participants will be identified through GP registries and social service records in the participating municipalities. There is no randomization or blinding, given the observational nature of the study. Recruitment will be coordinated by GPs and social workers, who will provide information sheets and collect written informed consent. We acknowledge that GP workload and the difficulty of reaching the most isolated individuals may represent practical barriers to recruitment. To mitigate these challenges, additional strategies will be implemented, including outreach activities through community organizations, collaboration with municipal health coordinators, and the use of snowball sampling when appropriate. These measures aim to maximize recruitment feasibility and ensure the inclusion of hard-to-reach populations.

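### The Discussion credits stratified sampling with supporting generalizability, but the sample-selection section describes no strata and no selection rule for the main sample

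*Protocol article*

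**What the plan says.** The strengths paragraph of the Discussion states: "The stratified sampling and use of validated instruments enhance the generalizability of findings". The wording is declarative, and it names two supports together: the sampling method and the instruments.

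The section headed Characteristics of participants and sample selection is where the article sets out how people enter the study. It says: "Eligible participants will be identified through GP registries and social service records in the participating municipalities". It continues: "Recruitment will be coordinated by GPs and social workers, who will provide information sheets and collect written informed consent". Because GP workload and isolation may hamper recruitment, it adds "outreach activities through community organizations, collaboration with municipal health coordinators, and the use of snowball sampling when appropriate".

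The limitations paragraph of the Discussion then concedes that voluntary participation may leave more fragile people under-represented, and that difficulty in reaching the most isolated may limit territorial coverage.

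**The concern.** Stratified sampling has a definite meaning. The population is divided by stated variables, people are selected within each division by a stated rule, and the estimates respect that structure. The Discussion relies on this property, while the section that should contain it describes recruitment through local professionals plus referral chains.

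This matters because the study is descriptive. It aims at prevalence estimates of unmet needs and access barriers, territorial maps of service gaps, and input to resource allocation. How far the results carry beyond the participants is central to their use. A reader who meets the stratification claim just before the limitations may think that a design feature offsets the conceded under-representation of fragile and isolated people. The article describes no such feature.

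**Working it through.** The question is one of consistency, so the check compares the Discussion claim with every place that could support it.

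1. **Sample selection.** The sources are registries and records, the recruiters are GPs and social workers, and the supplements are outreach, coordinators and "the use of snowball sampling when appropriate". No stratification variable, quota or rule for choosing individuals is given. Snowball referral has no known selection probabilities, so as described it cannot form part of a stratified probability sample.

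2. **Choice of areas.** The section on aim, design and setting defines which municipalities count as underserved (population density, drive time, service availability, socioeconomic vulnerability) and says: "These operational criteria ensure transparency and replicability in the selection of recruitment areas". These are eligibility conditions for areas. They do not divide the sampled population into strata.

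3. **Qualitative subsample.** Study procedures and outcomes asks for diversity in age, sex, chronic condition and isolation. This is the nearest thing to strata in the article, but it covers only the purposive interview subsample of about 40–50 and not the main sample.

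4. **Sample size.** Inputs from that section: prevalence p = 0.30, margin d = 0.05, 95% confidence (z = 1.96), loss 20–25%.
   - n = z² × p(1 − p) / d² = 3.8416 × 0.21 / 0.0025 = 322.7, so 323.
   - With 20% loss: 323 / 0.80 = 403.75, so 404.
   - With 25% loss: 323 / 0.75 = 430.7, so 431.

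   Both results lie within the stated range ("we aim to enroll approximately 400–500 participants"), so the figure reproduces. The formula is for a single unstratified proportion, with no allocation to strata. It neither supports the stratification claim nor depends on it.

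5. **Statistical analysis.** Prevalence estimates, bivariate tests and regression models are planned, with no mention of strata. On its own this would prove little, since weighting detail can be left to an analysis plan. It simply adds no support.

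6. **The sentence on randomization.** The article says: "There is no randomization or blinding, given the observational nature of the study". This concerns allocation and blinding. It is not evidence on whether people are sampled at random, and the point does not rely on it.

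Result: one sentence in the Discussion asserts stratified sampling. No other section describes it, and the section responsible for it describes another scheme.

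**The case against.** The strongest reply is that this is one phrase in a strengths paragraph. The sample size, outcomes and analysis do not use it. The sentence also credits validated instruments, and the next paragraph discloses the risk to representativeness. The article is a condensed version, so the full protocol might define strata. Much of this stands, and it limits the weight of the point. It does not remove the point: validated instruments support measurement rather than representativeness, and the article does not merely omit its sampling method but describes one and claims another.

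Some stronger readings are tempting, and the document does not support them.

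- **That the ±5-point margin falls with the phrase.** The sample-size calculation never appeals to strata, so keeping or deleting the phrase leaves it unchanged. Whether such a margin suits a non-probability sample is a separate question.
- **That barrier prevalence will be biased downward because people who see their GP are over-represented.** Eligibility requires registration with a GP, not attendance, and social service records, outreach and snowball referral may draw in people with more barriers.
- **That the bias can be given a size.** Suppose, purely as assumptions, that isolated people are 30% of the population, with barriers in 45% of them and 25% of the rest. The truth is 0.30 × 45 + 0.70 × 25 = 31%. A sample with 15% isolated gives 0.15 × 45 + 0.85 × 25 = 28%; with 25% isolated, 0.25 × 45 + 0.75 × 25 = 30%; with 40% isolated, 0.40 × 45 + 0.60 × 25 = 33%. The error runs from −3 to +2 points and changes sign with an input that the article does not give.
- **That missing weights are an error in themselves.** They may be left to an analysis plan that is not shown.
- **That the study certainly has no stratification.** The article does not say how individuals are picked from the registries. The supportable statement is that its sampling section describes none.

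**Conclusion.** The inconsistency is real and should be corrected, but it is a modest point about what the study may claim and not a defect that undermines its conduct. As written, the generalizability statement rests partly on a sampling property that is absent from the design described. No numerical size attaches to it: the enrolment figure reproduces and is untouched, and neither the amount nor the direction of selection bias can be derived from the document. The conclusion assumes that the sample-selection section gives the scheme to be used. If the full protocol defines strata for the main sample, the error lies in that section instead, and the two still have to be reconciled.

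**What to change.** **Preferred.** In the Discussion, delete stratified sampling as a support for generalizability. Describe the main sample as non-probability. State that prevalence estimates describe the participants and may be biased in either direction for the wider population of chronically ill adults in these areas, in line with the limitations already conceded there. The cost is a wording change and a weaker generalizability claim. No extra participants or fieldwork are needed.

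**Alternative, only if stratified selection is truly intended.** Before recruitment starts, state in the sample-selection section the strata, including geographic isolation, and how people are selected within each. State also that people reached by snowball referral or outreach will be reported separately, and name a matching estimator in the statistical analysis section. Strata by age alone would not do, because they do not balance isolation, which is where the article itself expects difficulty. The article reports that recruitment had not begun at submission and provides for amendments to go to the ethics committee and the registry, so a route exists. This option has a real cost: selection within strata adds work for GPs, whose workload the article already names as a barrier.

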## Conclusions

The CAMP study protocol provides a structured and rigorous foundation for investigating chronic care needs in rural and underserved areas. Through its integrative methodology, it will generate multidimensional evidence capable of informing localized, patient-centered health strategies. The findings are expected to support the national agenda for proximity healthcare and offer transferable insights for health systems facing similar territorial inequities.
